Medical intervention has limited impact on disease progression or exercise capacity and evidence regarding the cost effectiveness of any therapeutic approach in bronchiectasis is scant [1]. Exercise and self management training, as a component of a pulmonary rehabilitation (PR) program is a well-established and effective intervention for patients with chronic obstructive pulmonary disease (COPD), leading to reductions in the incidence of acute exacerbations and reduced health care utilisation as well as improvements in exercise tolerance and HRQoL [12-16]. Although international guidelines for PR recommend the inclusion of patients with bronchiectasis within existing programs [12], there is a lack of evidence supporting this practice [17]. One study has compared exercise training with or without inspiratory muscle training to standard medical care [18]. While significant short-term improvement in exercise capacity was demonstrated, benefits in HRQoL were only achieved with a combination of whole body exercise and inspiratory muscle training. The clinical significance of these findings is unclear, as the administered intervention differed from current recommendations for PR [12,19]. Although inspiratory muscle training was applied as a form of airway clearance therapy (ACT) in this study [18], no beneficial effects on ease of sputum expectoration were demonstrated. The long term benefits of PR which incorporates exercise training and self management in ACT compared to standard medical care, on exercise capacity and dimensions of HRQoL, including fatigue, anxiety and depression remains unknown. Furthermore, evaluation of the efficacy of such an intervention on the incidence of acute pulmonary exacerbations of bronchiectasis may provide evidence to determine best practice guidelines in this patient population.

The primary aims of this study are to (1) determine the short and long term effects of an eight-week PR program consisting of supervised exercise training and self management education in ACT compared to standard care on exercise capacity and HRQoL; and (2) establish the effect of this intervention on the incidence of acute exacerbations over a 12 month period in patients with bronchiectasis. We hypothesise that patients who complete PR will have a higher exercise capacity and HRQoL compared to standard care and that these benefits will be sustained for up to six months. PR will also reduce the incidence of pulmonary exacerbations over 12 months.

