### Outcome measures

All outcome measures will be recorded at baseline, immediately following the intervention period (nine weeks) and at six and 12 months post completion of the intervention (Figure 1). Baseline data collection will include age, gender, body mass index, usual ACT if previously prescribed and MMRC scale for dyspnoea [20]. The number of acute pulmonary exacerbations per year in the previous two years will also be collated. An exacerbation will be defined as an increase in clinical signs and symptoms requiring alteration of medication, including antibiotic therapy according to participant recall and medical record review.

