### Primary outcome measures

The primary outcome measures are maximal exercise capacity and HRQoL. An independent assessor, blinded to group allocation will perform all outcome assessments following the intervention period (nine weeks, six and 12 months) which will be conducted over a two day period at each time point.

**a) Maximum exercise capacity **will be measured with the ISWT [29]. To allow for a learning effect, this test will be performed twice, with a 30 minute rest period in between each test. The primary outcome is the greatest distance walked. The ISWT has demonstrated a moderate to strong correlation with peak rate of oxygen uptake [30], has shown responsiveness to change following PR [12] and has been used in patients with non-CF bronchiectasis [18].

b) **HRQoL **will be measured using the CRQ (self-administered version) [31-33]. This disease-specific questionnaire has demonstrated responsiveness to change following PR [33]. The CRQ consists of 20 questions and assesses the domains of dyspnoea during activities of daily living, fatigue, emotional function and mastery, using a 7-point Likert scale and provides a total HRQoL score. A higher score indicates better HRQoL.

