### Statistical analysis

Data will be entered into SPSS (version 17.0; SPSS Inc; Chi) for analysis. Descriptive statistics will be used to examine the distribution and data that are not normally distributed will be transformed or analysed using non-parametric tests. Analyses will be conducted using an intention to treat principle. Repeated measures analysis of variance with planned comparison will be used to compare all continuous variables that are normally distributed. Significant results will be analysed using post hoc tests. Categorical variables will be analysed using the chi square statistic. Relationships between outcome variables will be analysed using correlation coefficients. The alpha level for all statistical analyses will be set at 0.05.

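### Two primary outcomes, three follow-up visits and one flat 0.05: with no primary contrast or either/both rule, the error rate of a positive finding is not fixed at 5%

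*Protocol article*

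**What the plan says.** Under Primary outcome measures the protocol states: "The primary outcome measures are maximal exercise capacity and HRQoL". These are the greatest ISWT distance and the CRQ. Sample size bases its calculation on the ISWT and the CRQ total score. Under Outcome measures everything is recorded "at baseline, immediately following the intervention period (nine weeks) and at six and 12 months post completion of the intervention", so each primary outcome has three post-baseline values.

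The aim in the Background is to "determine the short and long term effects of an eight-week PR program", with no single time point. The hypothesis expects higher exercise capacity and quality of life after rehabilitation and that "these benefits will be sustained for up to six months".

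Statistical analysis gives three relevant rules. The model is set by this sentence: "Repeated measures analysis of variance with planned comparison will be used to compare all continuous variables that are normally distributed". Follow-up testing is covered in one line: "Significant results will be analysed using post hoc tests". The significance level is the same throughout: "The alpha level for all statistical analyses will be set at 0.05". The section does not say which comparison is planned, which ANOVA effect counts as significant, or how results on the two primary outcomes combine. The Discussion says that if findings are positive, rehabilitation should become routine for all patients. It does not define positive.

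**The concern.** A trial with two primary outcomes needs a rule for combining them. If either may carry the claim, testing each at 0.05 gives more than a 5% chance that at least one is significant when rehabilitation does nothing. Three visits add further opportunities unless one contrast is primary or a test controls entry to the rest.

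This goes beyond silence that a fuller document could fill. The article fixes the same 0.05 for every analysis, which leaves no room for a split between the two outcomes. At stake is the practice recommendation in the Discussion: a significant result on one outcome at one visit could be called positive and used to support it.

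**Working it through.** **Inputs from the protocol.** Two primary outcomes; three post-baseline visits; 0.05 per analysis; 36 participants (18 per group) at 80% power for the primary outcomes; 64 to be recruited, set by exacerbations (difference 1.0, SD 1.4, 80% power).

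**Inputs assumed.** Two-sided tests; correlations between visits and between outcomes, for which the protocol gives no values.

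**Step 1: reproduce the protocol's own figure.** The protocol states no family-wise error rate. Its one fully specified calculation is the 64. With a standardised difference of 1.0/1.4 = 0.714, a two-sided t-test at 0.05 with 80% power needs 31.76 per group, so 32 per group and 64 in total. This agrees; a one-sided test would need only 50. So two-sided 0.05 is a fair reading.

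**Step 2: one test per outcome, either suffices.** For independent tests, 1 - 0.95² = 0.0975. Positive correlation between outcomes lowers this slightly.

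**Step 3: the ANOVA as written, read as a gate.** Trials with no treatment effect were simulated: four visits, 32 per group, two outcomes, between-visit correlation 0.5-0.85, between-outcome correlation 0-0.5, 40,000 trials per setting.

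| What counts as positive | Chance under no effect |
|---|---|
| Group-by-time test significant on either outcome | 9.0-9.8% |
| As above, plus a significant follow-up contrast at 0.05 | 7.2-7.9% |
| Group main effect or group-by-time test significant on either outcome | 17.4-18.6% |
| Any of six change-from-baseline contrasts, no gate | 21.9-24.0% |
| Group-by-time test significant on both outcomes | below 1% |

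**Step 4: six direct tests, no gate.** If independent, 1 - 0.95⁶ = 0.265. With correlated normal test statistics (400,000 draws), the rate is 23.0% at correlations 0.5 between visits and 0.3 between outcomes, and 17.2% at 0.8 and 0.5. Widening the assumptions to 0.3-0.9 between visits and 0-0.7 between outcomes gives 13.7-25.3%.

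**Step 5: errors favouring rehabilitation only.** Over that wider range the ungated rate is 6.8-13.2%, against a matching nominal rate of 2.5%.

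**Step 6: the both-outcomes rule.** The figure below 1% applies when neither outcome improves. If one outcome truly improves and the other does not, the error is the single-test rate on the other, up to 5%. That holds only with one test per outcome. If each outcome could succeed at any of three visits, the error on the null one would be up to 1 - 0.95³ = 0.143.

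**Step 7: cost in power.** The protocol gives no effect size for the primary outcomes. Eighteen per group at 80% power implies a standardised difference of 0.961. At that effect, 32 per group gives power 0.966 at 0.05 and 0.936 at 0.025.

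**The case against.** A reader might infer that the trial's false-positive rate is simply 17-23%, because six comparisons are each made at 0.05. The document does not support that. It plans a repeated measures ANOVA for each outcome, with post hoc tests following significant results, and nowhere states six separate tests. Read as a gate on the group-by-time test, this gives about 7-10%. The higher range also needs correlations that the document does not give, and it counts results favouring control.

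The gate is not secure, however. Planned comparisons are mentioned separately from post hoc tests and are ordinarily made without an omnibus gate. The text does not say which ANOVA effect opens the gate, and none is described for the non-parametric alternative. The higher range is therefore possible, but conditional.

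The hypothesis joins exercise capacity and quality of life with *and*, and the sample size names both. That fits a both-outcomes reading, under which error is controlled, but neither sentence is a success rule. The hypothesis also reaches only to six months, so it is doubtful that the 12-month contrasts were meant as routes to success. Following patients to 12 months is no contradiction in itself: the aim covers long-term effects, and exacerbations are counted over 12 months.

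Finally, an article may leave the exact contrast and post hoc correction to an analysis plan. That is fair for those details, but it does not remove the stated rule of 0.05 for all analyses.

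**Conclusion.** The point stands as a gap in the success criterion combined with a flat alpha. If either outcome suffices, the two-sided family-wise error is about 7-10% under the gated reading. It is about 17-24% if visits are tested directly or if either ANOVA effect counts, under the correlations assumed above. It is held to 5% only under a both-outcomes rule with one test per outcome, which the document does not state. No single figure can be given as the trial's error rate, because the text does not settle which reading applies. The finding that 5% is exceeded under the either-outcome reading does not depend on the assumed six-test scenario: even one test per outcome gives up to 9.75%.

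**What to change.** Amend Statistical analysis before any unblinded analysis.

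1. Name one primary between-group contrast per outcome: for example the nine-week difference, or the group-by-time test if the short- and long-term aim is to stay primary.
2. Replace the flat 0.05 with Holm across ISWT and CRQ total at a family-wise 0.05. Alternatively, state that both must be significant, each at 0.05.
3. If nine weeks is primary under the Holm option, test six and then 12 months in fixed order within each outcome at that outcome's allocated level, for example 0.025. Testing them at 0.05 in each outcome would again allow up to 9.75%; at 0.025 the figure is 1 - 0.975² = 4.9%. An outcome's 0.025 must not be spent twice. It should pass to the other outcome only after its own sequence is complete; otherwise one null test at 0.05 and another at 0.025 could together reach 0.075.
4. Report the remaining outcomes as estimates with confidence intervals, without confirmatory claims.

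The change is wording only and needs no more participants. Power per outcome with 32 per group falls from about 97% to 94% at 0.025. Under the both-outcomes rule, the chance of succeeding on both is at least 0.966 + 0.966 - 1 = 0.932. These figures assume the 0.96 SD effect implied by 18 per group and make no allowance for dropout. Choosing nine weeks makes the long-term effect secondary, so that choice belongs to the investigators; what matters statistically is that one contrast is fixed in advance.

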## Discussion

Bronchiectasis has a heterogeneous clinical profile, secondary to the multiple aetiologies from which it may originate [1,7]. Although the precise global prevalence is unknown, bronchiectasis remains a cause of excessive morbidity [8]. In the current climate of limited health resources, it is important to provide interventions which not only contribute to improved HRQoL, but positively impact on disease progression and prognosis.

This research will be the first intervention study evaluating the short and long term efficacy of PR, including exercise training and self-management in ACT compared to standard care, in patients with non-CF bronchiectasis. Currently, progression of respiratory symptoms is evident in this heterogenous population despite optimal medical intervention [8]. We recently found that symptoms of chronic cough, sputum production and fatigue, based on the St George's Respiratory Questionnaire were associated with reduced exercise capacity in patients with mild to moderate bronchiectasis [41]. This implies that strategies such as a PR program which incorporates self management and adherence to ACT may have an equally positive impact on both diminished exercise capacity and clinically relevant dimensions of HRQoL, both of which will be important outcomes for all patients with bronchiectasis. Given the relationship between exacerbation rate and decline in pulmonary function [11], it would be highly significant if PR were to impact on the incidence of acute exacerbations in bronchiectasis. As both declining respiratory function and reduced physical activity are associated with increased mortality in this population [42], achieving a reduction in the incidence of pulmonary exacerbations would result in PR being one of the few available treatments with the potential to modify the disease course and prognosis in bronchiectasis and may be an inexpensive complement to existing medical care.

The results of this study will assist in the development of physiotherapy guidelines for the treatment of patients with bronchiectasis in clinical practice. While a recent survey revealed that the majority of physiotherapists in Australia and New Zealand routinely prescribed a form of ACT for patients with bronchiectasis, recommendations for exercise training were inconsistent [43]. In addition, no specific guidelines exist to guide clinicians in exercise prescription and the role of self management in ACT for patients with bronchiectasis. If the study findings are positive, the application of PR should be routinely instituted for all patients.

## Abbreviations

ACT: Airway clearance therapy; AQOL: Assessment of Quality of Life; CF: Cystic fibrosis; COPD: Chronic obstructive pulmonary disease; CRQ: Chronic Respiratory Questionnaire; FEV_1_: Forced expiratory volume in one second; FVC: Forced vital capacity; HADS: Hospital Anxiety and Depression Scale; HRQoL: Health related quality of life; ISWT: Incremental shuttle walk test; LCQ: Leicester Cough Questionnaire; MMRC: Modified Medical Research Council; PR: Pulmonary rehabilitation; RCT: Randomised controlled trial; 6MWD: Six-minute walk distance; 6MWT: Six-minute walk test.
